#### Secondary outcome: Quality of life

There has been an increased recognition of the importance of measuring the quality of life of children and young people with chronic health conditions as a standardized way of measuring treatment effectiveness within the child’s functional context (Haverman, Limperg, Young, Grootenhuis, & Klaassen, 2017; Silva, Crespo, Carona, Bullinger, & Canavarro, 2015; Wright & Majnemer, 2014). Measuring quality of life in a validated and standardized way allows for evaluating both intervention effectiveness and cost effectiveness (Aledort et al., 2012).

The Pediatric Quality of Life (PedsQL™; Farias Queiroz, Costa Amorim, Zandonade, & Monteiro de Barros Miotto, 2015)) inventory is a widely used and validated modular measurement of health-related quality of life. It has been designed to measure the core dimensions of health as delineated by the World Health Organization, including school functioning. The 23-item measure covers four domains: physical functioning, emotional functioning, social functioning, and school functioning. It has both self-report and parent proxy report versions, and can be scored so as to obtain a total scale score or summary scores for physical health and psychosocial health. However, scale scores for each of the four domains have been used in previous research of children and young people with chronic illnesses (Farias Queiroz et al., 2015). There are age specific versions for 5–7 yo, 8–12 yo, and 13–18 yo children and young people.

### Blinding

Blinding refers to keeping study participants and personnel “unaware” of which study group they belong to (i.e., intervention group or no-intervention/control group). Blinding in controlled studies is considered an important strategy for minimizing the potential of any performance or detection bias. However, blinding of personnel and participants is often difficult when evaluating psychosocial interventions (Montgomery et al., 2013), and blinding of both groups is considered not achievable in the current study.

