## Method

### Study Design and Setting

Many researchers (e.g., Chalmers, 2005; Gray, 2001; Littell & Shlonsky, 2010; Shlonsky & Gibbs, 2004) consider the randomized controlled trial (RCT) the “gold standard” in effectiveness evaluations as it is viewed to be the best design for minimizing the influence of bias. But for many others in the pedagogical community, the debate on this point is still open (Biesta, 2007). In our circumstance, given that access to a quality education is a right of the child along with the potential public sensitivity of randomly allocating hospitalized children and young people to either receive education support or not while in hospital, an RCT may not be considered either appropriate or ethical.

Fortunately, other controlled study designs are available for consideration. Controlled studies (i.e., studies with both an intervention group and a well-matched non-intervention or control group) are considered best for evaluating the effectiveness of an intervention because they state the counterfactual. That is, they investigate and compare both what happens if a group of people receive the intervention and what happens if a group of people don’t receive the intervention. This, in turn, allows stronger and more robust claims of causality and effectiveness of a given intervention; that is, that any differences in results between the two groups were due and can be attributed to the intervention (Chalmers, 2005; Shlonsky & Gibbs, 2004).

One such design is that of a controlled cohort study, where both the intervention group and the control group exist “naturally” in the community. Such is the case in Victoria, Australia, where the Department of Education and Training (DET) funds education support programs at some, but not all, pediatric hospitals and departments. The DET funds education programs at two pediatric hospitals (Royal Children’s Hospital and Monash Children’s Hospital), but not four regional pediatric departments in hospitals in Warrnambool, Ballarat, Gippsland, and La Trobe. Children and young people with chronic illnesses admitted to the latter hospitals where there is no funded education support program, therefore, naturally form the control or comparison group.

The subjects for the current study consisted of the children and young people under treatment for a chronic health condition at the Royal Children’s Hospital (the intervention group) and the four regional hospitals.

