### Outcomes, Confounders, and Measurement Instruments

#### Primary outcome: Engagement in education and learning

We will use a short form of the validated Attitudes to School Survey developed by Khoo and Ainley (2005) and used in the *Longitudinal Study of Australian Children*. The survey has been used and referred to by the authors as a measure of school engagement as it aims to measure aspects of the complex relationship between engagement, attitudes, and motivation in terms of their influence on intentions to participate in school and schoolwork. The survey includes a primary and a secondary school version each consisting of 30 statements that cover 5 domains: students’ general satisfaction with school, their motivation, their attitudes toward their teachers, their views on the opportunities their school provides, and their sense of achievement. Students are asked to indicate their level of agreement on a 4-point Likert scale ranging from *strongly agree* to *strongly disagree*.

*General Satisfaction*, sometimes called positive affect, reflects favorable feelings about school as whole. A typical item is *my school is a place where I really like to go each day*.*Motivation* represents a sense of self-motivation in learning and that learning is enjoyable for its own sake. A typical item is *my school is a place where I get excited about the work we do*.*Achievement* reflects a sense of confidence in one’s ability to be successful in school. A typical item is *my school is a place where I am good at schoolwork*.*Opportunity* represents a belief in the relevance of schooling for the future. A typical item is *my school is a place where what I learn will be useful*.*Teachers* refers to a feeling about the adequacy of the interaction between teachers and students. A typical item is *my school is a place where my teacher listens to what I say*.

We have developed a short form (15 statement) version, anticipating that the full version would be potentially too burdensome for the hospitalized and chronically ill child or young person. Items were chosen on the basis of their face validity/perceived appropriateness by the author, who had more than three years’ experience working with hospital-based teachers/educators and young people at the Royal Children’s Hospital in Melbourne, Australia, 2012–2016.

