#### 3-month and 6-month data

We will collect primary and secondary outcome data at both the 3- and 6-month time points post the time of baseline data collection.

In addition, we will collect information on the number and type of education support activities (as described in the program logic model; see Figure 2) that were received by the young person, his or her parent/s, and the school for both the intervention and control groups.

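### The Blinding section names detection bias, reasonably says participants and personnel cannot be blinded, and then adopts no safeguard for data collection or analysis, although both outcomes are subjective questionnaires

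*Protocol article*

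**What the plan says.** The Blinding section defines its subject narrowly: "Blinding refers to keeping study participants and personnel “unaware” of which study group they belong to". It gives the purpose: "Blinding in controlled studies is considered an important strategy for minimizing the potential of any performance or detection bias". It notes that psychosocial interventions are often hard to blind and ends with the statement that "blinding of both groups is considered not achievable in the current study". In context, the two groups meant are personnel and participants. People who collect, score or analyse data are not discussed, and no other protection is named.

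Other sections bear on this:

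- Study Design and Setting describes a cohort design "where both the intervention group and the control group exist “naturally” in the community". The intervention arm is one hospital with a funded programme; the control arm is four regional hospitals without one.
- For the primary outcome, "Students are asked to indicate their level of agreement on a 4-point Likert scale". Scale scores will be calculated both for the domains and for the whole survey.
- Secondary outcome: Quality of life describes an instrument with self-report and parent-proxy versions, and with total, summary and domain scores. It does not say which will be used.
- Baseline data allows either the lead researcher or a hospital-based educator to collect baseline data, which include both outcomes.
- 3-month and 6-month data names no collector and no main time point. It adds that "we will collect information on the number and type of education support activities", in both groups.
- Data Analysis uses those activity data as a measure of dose in a sensitivity analysis.

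**The concern.** When participants cannot be blinded and report their own outcomes, the protections that remain are how the answers are collected and how they are analysed. The section stops before reaching either.

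Two separate risks follow. The first arises at collection. If the person handing out an attitude-to-school questionnaire works for the programme under evaluation, and works only at the intervention hospital, the setting in which children answer differs by arm. The second arises at analysis. Someone who knows the arms, and can still choose score level, reporter and time point, can favour one result without meaning to.

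Adjustment for family socio-economic position, parental involvement and parental distress removes neither risk. Effectiveness is the first listed aim, and the procedures are meant to inform a larger study, so a weakness accepted here is likely to be copied.

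**Working it through.** **1. The plan's own sample size.** Sample Size and Power Analysis gives 0.3 SD, 80% power, 180 complete per arm and 25% attrition. It states no significance level; I assume two-sided 5%.

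n per arm = 2 × (1.96 + 0.842)² / 0.3² ≈ 174.5, rounded up to 175, against 180 stated. This is close enough to count as reproduced. 180 / 0.75 = 240, as stated. The feasibility study recruits 40 per arm, so at the same attrition 40 × 0.75 = 30 complete. The point does not depend on these figures; they only set the scale for step 4.

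**2. Stated purpose against adopted safeguards.**

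| Stage | What the article says | Safeguard adopted |
|---|---|---|
| Participants and personnel | Blinding not achievable | None; reasonable |
| Baseline collection, including outcomes | Lead researcher or hospital-based educator | None |
| Collection at 3 and 6 months | Collector not named | None |
| Scoring and analysis | Not mentioned under Blinding | None |

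The control hospitals have no funded education programme. A hospital-based educator is therefore likely to be available only in the intervention arm. That is an inference from two sections, not a statement in the article.

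**3. Choices open in the text.** Domain or whole-survey score, self or proxy report for quality of life, and 3 or 6 months. Each could be settled after arm-labelled data have been seen.

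**4. Scale of respondent bias, as an assumed illustration.** The documents give no figure. Suppose a pure reporting shift b in SD units, no true effect, independent children and a two-sided 5% test.

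SE = √(2/n); chance of a significant result = P(|Z + b/SE| > 1.96).

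| Complete per arm | SE | b = 0.10 | b = 0.20 |
|---|---|---|---|
| 30 (this study) | 0.258 | 6.7% | 12.1% |
| 180 (a full-size study) | 0.105 | 15.8% | 47.5% |

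Relative to the 0.3 SD target, these shifts are 0.10/0.3 = one third and 0.20/0.3 = two thirds.

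**5. What each safeguard can change.** The shift in step 4 is in the answers. Coding the arms A/B leaves every number in that table as it is. Masked analysis acts only on step 3. A common mode of collection and a collector from outside the programme act on the part of the shift that arises when the questionnaire is filled in, and the documents do not show how large that part is.

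**The case against.** The strongest reply is that the section is right about what it addresses. Under Intervention to Be Tested, the learning plan is prepared with the student and family, and Table 1 has programme staff consulting families. These families know they receive support. This stands.

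A reader might infer that the article abandons blinding altogether, or that its own design contradicts it because nobody is allocated. The text supports neither. Only participants and personnel are called impossible to blind; masked analysis is unmentioned, not ruled out. Naturally formed groups do not make families unaware of their care. Nor can it be said that the Plain Language Statement reveals the contrast, since it is not shown, or that families will be questioned about programme activities, since those data could come from records.

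It is also fair to say that scoring fixed-response items leaves little room for judgement, that masked analysis cannot repair biased answers, and that the author's selection of items for the short form ("Items were chosen on the basis of their face validity/perceived appropriateness by the author, who had more than three years’ experience") applies equally to both arms.

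Finally, a condensed article may leave question order and arm coding to fuller documents. That limits the point but does not remove it. The article gives blinding its own section, cites detection bias, and closes the matter without any safeguard. It also states outright that a hospital-based educator may collect outcome data.

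**Conclusion.** The point holds in a limited form. The statement about participants and personnel should stay. The weakness is that the section recognises detection bias and adopts nothing against it, while outcomes are subjective, collection may differ by arm, and several analysis choices are open.

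The size is unknown. Under the assumed shift of 0.10 to 0.20 SD, false positives at 30 completers per arm rise from 5% to about 7% to 12%. The larger figures at 180 per arm describe a study that this protocol will not run. A reader might take any of these figures as the gain from masking the analysis; they are not. They describe bias in the respondents' answers, which masked analysis leaves untouched.

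For a feasibility study of 40 per arm this is a modest point. It is worth acting on because the measures are cheap and this is the stage at which to try them.

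**What to change.** Keep the statement on participants and personnel and add to the Blinding section:

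1. **Collection.** At baseline, 3 and 6 months, the engagement and quality-of-life questionnaires are completed in the same self-completed mode in both arms, with the same age-appropriate help for the youngest children. They come before any question on education support activities and are not administered by programme educators. Amend Baseline data to agree.
2. **Analysis.** Scoring and the primary outcome models are fixed and run with arms coded A/B and site labels withheld. The code is opened only once score level, reporter, time point and model are locked. The dose sensitivity analysis, whose data would largely reveal the arm, is run afterwards.
3. **Limitation.** Expectation bias in self-reported answers cannot be removed by masked analysis and is acknowledged when results are interpreted.

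The cost is protocol wording, a fixed questionnaire order and a recoded group variable, with no extra participants or visits. There are two small downsides. Masking is imperfect because one arm is a single hospital, and the lead researcher must do the collection at the intervention site instead of sharing it with educators.

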### Data Collection

#### Baseline data

Baseline data will be collected by the lead researcher or hospital-based educator at the time of student recruitment to the study or within one week of recruitment. It will consist of basic demographic data of the young person (age, gender, school grade/level, type of chronic illness, cultural identity, main language spoken at home) and of the parent (socio-economic position, involvement in child’s education, and psychological stress). We will also collect baseline data on the primary and secondary outcomes using the measures described above.

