### Participants

Participants will need to meet the following eligibility criteria:

Being school aged (5–17 years old)Having a chronic illness (for example, but not limited to, cancer, cystic fibrosis, eating disorder and Crohn’s disease/renal failure)Having an expected length of stay (LOS) in hospital of five or more days in a six-month period

The criterion of an expected LOS of 5+ days was informed by the work of [name] and colleagues, whose Australian research investigated the impact of school absence on academic performance. Their study (Hancock, Shepherd, Lawrence, & Zubrick, 2013) was based on students who were enrolled in the public school system in Western Australia from 2008 to 2012. The data included information collected by schools on students and their caregivers upon enrolment, attendance records, and the results of the National Assessment Program – Literacy and Numeracy (NAPLAN). The authors hypothesised a threshold effect of absence from school on academic performance, such that a small amount of absence from school might have minimal effect on academic performance, but beyond some threshold attendance level there would be a noticeable drop in measured academic performance. Their findings, however, generally support the notion that “every day counts.” That is, every day of absence from school is associated with progressively lower achievement in numeracy, writing, and reading.

They also found that, generally, an absence of four weeks per half year resulted in performance dropping to that of the national minimum standard. However, school absence had a much greater influence on the achievement of students in lower socio-economic index schools with absences of three weeks per half year resulting in performance dropping to that of the national minimum standard.

In earlier research on categories of at-risk attendance, again in the Western Australian school jurisdiction and based on empirical findings from the 1993 Western Australian Child Health Survey (WACHS), Zubrick, Silburn, Gurrin, and Shepherd (1997) found that students who were, on average, absent for two weeks per half year would be considered to be at-risk for lower academic competence.

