### Intervention to Be Tested

The education support program at the Royal Children’s Hospital (RCH) in Australia is funded by the Victorian DET and employ qualified teachers to work with hospitalized young people/students to help maintain engagement with the students’ regular schools and peers, and engagement in education and learning. The Education Institute teachers evaluate new patients to determine the appropriate level of educational support. Evaluations are based on need or educational risk, with eligible students being offered individual or group learning sessions, or a combination of both. Each student receives an Individual Learning Plan (ILP) prepared in collaboration with the student, families/carers, and the enrolled educational setting. The ILP is reviewed regularly and updated in line with the student’s educational progress. The hospital kindergarten program is led by qualified early childhood educators who, through engaging play-based learning, help prepare children for school. To be eligible for the program, children must be at least 4 years old before April 30 in the year of enrolment. The Education Institute offers an evidence-based program built on high-impact teaching strategies, with a focus on literacy and numeracy underpinned by the Victorian Curriculum.

Elements of the education support program are described in a program logic model developed in consultation with staff from the Centre for Program Evaluation at the University of Melbourne. It depicts a socio-ecological approach that recognizes the influence of a number of spheres within which the child functions on a daily basis (Bronfenbrenner, 1995). These include the spheres or levels of the individual, family, schools, community and service systems. (For more detail, see Figure 2: Logic Model of an Education Support Program for Children and Young People with a Chronic Health Condition; Barnett, 2018.) The key activities and variables of the intervention across the first three spheres are listed in Table 1. Finally, the education support model at the RCH also reflects the five common themes of pediatric hospital-based education support programs as described in the introduction.

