**Figure 2 F2:**
[figure not shown]
Logic Model of an Education Support Program for Children and Young People with a Chronic Health Condition.

**Table 1 T1:** Key activities of education support programs for hospitalized students with chronic health conditions.

Sphere of influence/level	Key activities of education support

Individual young person	Assist children stay connected to their school, teachers and peers Develop/Implement an Individual Learning Plan (ILP) Deliver group and one-to-one learning opportunities Use inquiry/problem solving strategies to explore student’s passions about real world topics
Family	Meet and consult with families about their child’s learning needs Support parents as advocates of their child’s right to education Meet and consult with families about their coping Provide parents with information, resources & referrals
School	Liaise with teachers so the child’s learning needs continue to be identified and met throughout their healthcare journey: hospital, home and return to school Together with the healthcare team, assist schools prepare for the child’s transition back to school: workshops with teachers and peers

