### Recruitment and Consent

Approval to undertake the feasibility study will be sought from the Victorian DET. Once such approval has been obtained, all five pediatric sites (one pediatric hospital as the intervention site and four regional hospitals with pediatric wards as the control sites) will be approached by the lead researcher and invited to participate in the feasibility study. Once consent has been obtained from these two levels, we will proceed with the rolling recruitment of individual young people. Specifically, all new inpatients as they present to hospital and who meet the eligibility criteria will be approached by the lead researcher and asked if they would participate in the trial. Both the young person and his or her parent/s or caregiver/s will receive a Plain Language Statement about the study and asked to provide written consent.

For aim number 4 (Obtain feedback from stakeholders about the feasibility of the above with the view of conducting a larger scale trial), we will identify two key stakeholders at each of the five locations and ask them to participate in semi-structured interviews with the lead researcher. The purpose of the interviews will be explained, and verbal consent will be obtained and recorded by the lead researcher.

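### Baseline may be collected up to a week after recruitment and need not precede first contact with the education programme, so it can be post-exposure at the intervention hospital but essentially not at the control sites

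*Protocol article*

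**What the plan says.** All references are to the protocol article.

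- **Baseline window (Baseline data).** Baseline is taken "at the time of student recruitment to the study or within one week of recruitment". On who takes it: "Baseline data will be collected by the lead researcher or hospital-based educator".
- **Content of baseline (Baseline data).** For the parent it includes "socio-economic position, involvement in child’s education, and psychological stress". For the child: "We will also collect baseline data on the primary and secondary outcomes using the measures described above".
- **Recruitment (Recruitment and Consent).** Recruitment is rolling: "all new inpatients as they present to hospital and who meet the eligibility criteria will be approached by the lead researcher".
- **Start of the programme (Intervention to Be Tested).** "The Education Institute teachers evaluate new patients to determine the appropriate level of educational support". Eligible students are then offered sessions, and each receives a learning plan. None of this is tied to completion of baseline.
- **Family activities (Table 1).** One is "Meet and consult with families about their coping". Another is supporting parents as advocates for their child's education.
- **Eligibility (Participants).** "Having an expected length of stay (LOS) in hospital of five or more days in a six-month period".
- **Analysis (Confounders; Data Analysis).** Outcomes are analysed by ANOVA with control for the named confounders: socio-economic position, parental involvement in education, and parental mental health measured by the DASS-21. The child's baseline score is not named as a covariate.

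**The concern.** A baseline measure serves as a baseline only if it is taken before exposure. Here a new inpatient at the intervention hospital can be recruited on arrival, assessed by programme teachers, start sessions, and only then complete the questionnaires, all within the stated rule. The control sites have no funded programme, so the same delay there brings essentially no exposure. Any contamination of baseline is therefore one-sided.

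Three things are at stake.

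1. **Comparability.** Without randomisation, the baseline data are the main evidence that the two groups are alike. If one group is measured after exposure, a pre-existing difference and an early programme effect cannot be told apart. This holds whatever model is fitted.
2. **Adjustment for possible mediators.** The article commits to controlling for parental stress and involvement. Both are measured at this same baseline, and the programme's family activities are directed at coping and at parents' role in their child's education. Adjusting for them after exposure may remove part of the programme's effect.
3. **The child's own baseline score.** If this were used as a covariate or for change scores, early benefit would be partly or wholly subtracted.

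A late baseline cannot be recovered afterwards, and the larger study may inherit the rule.

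**Working it through.** **Step 1. Timing.** The window runs from 0 to 7 days after recruitment. The stay criterion is an expected 5 or more days, accumulated over six months. The window can thus exceed the minimum qualifying stay by 7 − 5 = 2 days. Because the days accumulate, a single admission may be shorter than five days. Recruitment happens on presentation and programme assessment applies to new patients, so the window and the start of the programme overlap. No section sets their order.

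**Step 2. The article's own figure.** Sample Size and Power Analysis gives 180 complete cases per arm for 80% power at 0.3 SD, and 240 recruited after 25% attrition. Taking a two-sided 5% level (not stated in the article):

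- n per arm = 2(1.96 + 0.84)² / 0.3² ≈ 175 (176 with the t distribution), against 180 stated;
- 180 / (1 − 0.25) = 240.

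The figures reproduce and are not in dispute. The 0.3 SD is used below only as a yardstick.

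**Step 3. Route through the parent measures (the adjustment that is stated).** If early contact shifts a parental covariate by δ and the covariate has within-group slope β on the outcome, adjustment changes the estimate by −βδ. The documents give neither β nor δ, so no figure is possible. The measures differ in how far a few days could move them:

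| Measure | Scope for movement within a week |
|---|---|
| Socio-economic position | None |
| Help with homework (this school year) | Little |
| Contact with the school (last 12 months) | Little |
| Talking about school activities | Some; no long recall period stated |
| DASS-21 | Some; no long recall period stated |

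**Step 4. Route through the child's baseline score (conditional; not stated in the article).** Let f be the share of the 0.3 SD effect already present at baseline in the intervention group, and r the correlation of baseline with follow-up, with equal SDs at both times. The expected baseline difference due to the programme is 0.3f. Baseline-adjusted analysis (ANCOVA) subtracts r times that difference; a change score subtracts all of it:

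- ANCOVA estimate = 0.3 − r × 0.3f = 0.3(1 − rf)
- Change-score estimate = 0.3(1 − f)

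| f (assumed) | ANCOVA, r = 0.4 | ANCOVA, r = 0.6 | ANCOVA, r = 0.8 | Change score |
|---|---|---|---|---|
| 0 | 0.300 | 0.300 | 0.300 | 0.300 |
| 5% | 0.294 | 0.291 | 0.288 | 0.285 |
| 20% | 0.276 | 0.264 | 0.252 | 0.240 |

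Example: f = 20%, r = 0.8 gives 0.3 × (1 − 0.16) = 0.252 SD. If baseline precedes first contact, f = 0 and there is no loss by this route.

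**The case against.** **The main harm depends on an analysis the article does not describe.** A reader might infer that early benefit is certain to be taken out of the estimate. The documents do not support this. Data Analysis commits only to controlling for the named confounders, and the child's baseline engagement and quality of life are not among them. If group means at 3 and 6 months are compared, early gain in the child's score is not subtracted. This objection stands, and Step 4 is conditional for that reason.

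**The stated adjustment is little affected.** Two of the three involvement items look back over a school year or 12 months. This limits the second consequence mainly to the DASS-21 and one involvement item, but does not remove it.

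**The loss may be trivial.** A week is about 8% of three months (7/91), and baseline at recruitment is the first option, with one week as the outer limit. A reader might infer a serious loss of power for the larger trial. That is not supported either: f is unknown, and pairing a change-score effect with a raw-score SD of 1 overstates the loss. At r = 0.6 the change-score SD is √(2 × 0.4) = 0.894 and the ANCOVA residual SD is √(1 − 0.36) = 0.8. Even if one third of the effect were present at baseline, ANCOVA with 180 per arm would have a standardised effect of 0.24/0.8 = 0.30, the planned value.

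**The stay criterion is not the exposure period.** A reader might infer that the whole intervention can be over before baseline. The criterion is an eligibility floor, and Table 1 extends support to home and the return to school. The point is that some exposure can come first, not all of it.

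**Support activities are recorded.** The article counts number and type of activities in both arms and uses them as dose. That helps, but they are not said to be dated relative to baseline or to cover earlier admissions, so they cannot identify a contaminated baseline.

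**Conclusion.** The point holds as a weakness in a stated rule. Followed as written, the plan can yield baseline outcomes and parental measures that are post-exposure at the intervention hospital and essentially pre-exposure at the control sites. The loss of clean baseline comparability does not depend on the analysis model. Some adjustment for early programme effects through parental stress and, to a lesser degree, involvement is possible under the stated analysis; its size cannot be computed from the documents. Bias towards no effect through the child's own score arises only if that score is used as a covariate or for change scores. In that case a 0.3 SD effect would be estimated by ANCOVA as about 0.29 SD at f = 5%, or 0.25 to 0.28 SD at f = 20%, for r from 0.4 to 0.8. Both f and r are assumptions, and the true loss may be small.

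This is a cheap improvement worth making before the study starts, not a demonstrated fatal flaw.

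**What to change.** Replace the timing rule in Baseline data with:

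*Baseline child and parent questionnaires are completed at consent and before the first education-support contact of that admission, with the same time from admission at all five sites. The date of first contact and any earlier hospital education support are recorded. Late baselines are flagged and excluded in a sensitivity analysis.*

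The change concerns when questionnaires are completed and what is recorded; eligibility stays as it is, and children with earlier exposure are not excluded.

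Cost: a short change of text and two form fields (date of first education contact, earlier hospital education support). The downside is slightly tighter logistics on admission and a few late baselines set aside in the sensitivity analysis.
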